## Abstract

**Background:**

Tuberculosis (TB) prevention is a major goal in teaching hospital setting. Because of the possible progression or reactivation of latent disease, the screening of both health-care workers (HCWs) and students is an important issue in the TB control program.

**Objective:**

to deploy a web-based platform interoperating health surveillance systems from different hospitals to define models based on the highlighted risk factors to predict the occurrence of Latent Tuberculosis Infection (LTBI) and to define prevention strategies and interventions.

**Methods:**

This is a cross-sectional ambispective observational study without drug and device. The primary endpoint is the prevalence of LTBI. The secondary endpoint is the identification of possible risk factors of LTBI in a large cohort of HCWs and students.

**Conclusions:**

This study aims to enrich the primary prevention measures against TB, having a high socio-economic-health impact in high-risk populations (HCWs and students) through an interoperable digital approach based on data obtained in three large Italian teaching hospitals.

**ClinicalTrials.gov:**
NCT05756582

## Introduction

*Mycobacterium tuberculosis* (Mtb) may develop symptoms and signs of disease (TB disease), in a subset of subjects, or may have no clinical evidence of disease (latent tuberculosis infection [LTBI]) [1]. TB disease remains one of the major causes of morbidity and mortality in the world [1]. The WHO estimates that the annual incidence of tuberculosis has been raising worldwide from 10.0 million in 2020 to 10.6 million people in 2022 [1].

Mtb is transmitted from person to person via the airborne route [2]. Several factors determine the probability of Mtb transmission: (1) infectiousness of the source patient—a positive sputum smear for acid-fast bacilli (AFB) or a cavity on chest radiograph being strongly associated with infectiousness; (2) host susceptibility of the contact; (3) duration of exposure of the contact to the source patient; (4) the environment in which the exposure takes place (a small, poorly ventilated space providing the highest risk); and (5) infectiousness of the Mtb strain.

In 2021, a systematic review explored the status and risk factors of TB infection among HCWs through the evaluation of all published reports from 1 August 2010 to 31 December 2018. The TB infection rate in HCWs was higher than that of the general population. Based on 39 studies, the prevalence of TB in HCWs (tuberculin skin test positive) was 29.94%. In contrast, the global burden of latent TB infection was 23.0% (95% uncertainty interval: 20.4%–26.4%) in 2014. The risk factors of TB among HCWs were aging, long duration of employment, nursing professionals, lack of Bacillus Calmette-Guerin vaccination, and low body mass index [3].

In 2020, a meta-analysis examined population-level incident TB risk in a pooled data set of more than 80,000 individuals tested for LTBI in 20 countries with low M. tuberculosis transmission (annual incidence ≤ 20 per 100,000 persons). Cumulative 5-year risk of incident TB among people with untreated LTBI approached 16% among child contacts and approximately 5% among recent adult contacts, migrants from high TB-burden settings and immunocompromised individuals. Most cumulative 5-year risk was accrued during the first year among risk groups with an index exposure. The substantial variation in incidence rates even within these risk groups suggests that an individual-level approach to risk stratification is required. The first direct data-driven model was developed to incorporate the magnitude of the T cell response to M. tuberculosis with readily available clinical metadata to capture heterogeneity within risk groups and generate personalized risk predictions for incident TB [4].

Health-care workers (HCWs) are at higher risk of being exposed to tuberculosis compared to the general population [5], even in countries with low TB incidence, such as Italy. In these workers, the assessment of LTBI and TB disease is part of the annual health surveillance program aimed to prevent occupational diseases [6].

Because of the severity of their symptoms, individuals with an active contagious form of tuberculosis have a higher chance of being hospitalized and can remain for hours or days at the health care facility with a pending diagnosis.

For these reasons, the prevention of nosocomial transmission of tuberculosis represents prominent public health and occupational requirement [7,8]. However, it is also important to note that health-care providers (HCPs) may contract an infectious disease outside of the workplace, thus representing a source of infection to colleagues and patients that are more likely to be affected.

It is estimated that one patient with untreated active infectious pulmonary tuberculosis can affect 10–15 people within a year [9]. Of these individuals, a percentage between 3 and 10% will be infected, half of whom will become ill within one to two years while the others might develop the illness at any point of their residual life [7]. On average, 10% of people with LTBI develop TB disease in their lifetime, half of which become ill within 2 years after exposure [5,7,9]. About 70% of incident cases of TB are a result of the reactivation of a past infection [5,7,9,10], especially in countries with a low TB prevalence [11–13]. Furthermore, the pharmacological management of patients with TB can be complicated by drug-induced reactions [14].

For these reasons, the identification and prophylactic treatment of individuals with LTBI are crucial for the elimination of the disease. Health-care students involved in clinical training could be exposed to occupational risks like those of HCWs. Therefore, the screening for LTBI of both HCWs and undergraduate students attending teaching hospitals is recommended especially in low-incidence countries, including Italy, in order to obtain an early diagnosis of cases and prevent progression to active disease [8,15].

Despite the higher risk of TB infection reported in high TB burden countries among both HCWs and healthcare students compared to the general population [16,17], such TB control activities are difficult to be implemented in these settings [18].

According to Italian law [19,20], it is mandatory for employers to evaluate all risks in the workplace, including the risk of exposure to biological agents, and to implement measures to prevent the spread to operators or to limit the severity of its consequences. For this purpose, great importance is given to health surveillance of tuberculosis infection. In fact, the surveillance of LTBI in HCWs is considered fundamental for tuberculosis prevention.

Very few studies have investigated the epidemiology of TB infection among undergraduate healthcare students worldwide, and few, with a large sample, in areas with a low-incidence of TB [17,21–27].

The ongoing CROSSWORD study, aimed at collecting big data on the prevalence of LTBI in HCWs and students and the identification of possible risk factors for LTBI, in a single center, presents, as main current criticality, the monocentric nature of the study. The translation of the same methodologies of the CROSSWORD study within the research project entitled “*Implementing an interoperable web-based platform to support health surveillance against latent tuberculosis infection in health care workers and students to define prevention strategies and interventions: the evolution of CROSSWORD Study*” and the involvement of more centers will allow the creation of a shared interoperable digital platform and the definition of primary prevention strategies for LTBI.

Our research project is inspired by TB risk prediction model elaborated in a recent meta-analysis (PERISKOPE-TB) that combines a quantitative measure of T cell sensitization and clinical covariates [4]. We adopted some candidate predictors included in the final version of prognostic model described by Gupta et al.: exposure, HIV status and history of hematological or solid organ transplant [4].

Here we present the protocol of the Evolution of CROSSWORD study.

## Materials and methods

### The aim

The Evolution of CROSSWORD Study is an ambispective observational study aimed at: 1) estimating the prevalence of LTBI in HCWs and students attending University Hospitals with focus on the association between LTBI and potential risk factors, and 2) creating a web-based platform interoperating health surveillance systems from different hospitals to define models based on the highlighted risk factors to predict the occurrence of LTBI and to define prevention strategies and interventions.

### Design

The Evolution of CROSSWORD study includes a retrospective phase focused on the analysis of data derived from the ongoing CROSSWORD Study conducted at Fondazione Policlinico Universitario A. Gemelli IRCCS (FPG) and Università Cattolica del Sacro Cuore (UCSC) in Rome, Italy. The subsequent prospective phase will collect data from two centers in southern Italy, the University of Palermo (UNIPA) and the University of Bari (UNIBA)/ University Hospital of Bari. It is part of the national research project “DARE - Digital Lifelong Prevention”, funded by the Ministry of University and Research (MUR) as part of the National Plan for Complementary Investments to the PNRR, with the goal of maximizing the potential of data to enhance health promotion and enable lifelong prevention. DARE focuses on improving health trajectories by leveraging data. Furthermore, DARE Project aims to create a community focused on digital prevention through research, innovation, and engagement of all stakeholders [28].

With the support of the University of Bologna, partner of the national DARE project, the Research Team will then proceed with the analysis of the data collected at three clinical centers and the definition of a single data platform necessary for the assessment of the prevalence of LTBI and the identification of risk factors. Furthermore, prediction algorithms will be validated in all university hospitals involved through the recruitment of a new cohort of HCWs and students.

### Setting of the study

The participants will be recruited at: 1) the Health Surveillance Unit of Fondazione Policlinico Universitario A. Gemelli IRCCS, in Rome (FPG and UCSC), 2) the Department of Health Promotion, Maternal and Infant Care, Internal Medicine and Medical Specialties (PROMISE) of University of Palermo (UNIPA), 3) Dipartimento di Medicina di Precisione e Rigenerativa e Area Jonica (DiMePRe-J) of University of Bari (UNIBA) and 4) Unit of Occupational Medicine of University Hospital of Bari.

### The sample size

From the literature, Coppeta et al. [29] found a rate of LTBI prevalence of 2.1% in a population of Italian HCWs in Rome, and Verso et al. reported a prevalence rate of LTBI of 0.62% among Italian healthcare students and postgraduates in Palermo [26]. Therefore, we assumed a prevalence of LTBI of 1% in our population. The sample size was calculated considering the objectives of estimating the prevalence of LTBI and identifying its risk factors.

As regards the estimate based on the first outcome, considering 1) the assumed prevalence of LTBI of P = 1% in each teaching hospital involved in the research project, 2) an error estimate of d = 0.3%, and 3) a chosen confidence level of 90%, we obtained a total sample size of 2,977 subjects to be enrolled. The following formula [30] was used:

$$n=\frac{Z^{2}P\left(1-P\right)}{d^{2}}$$

where Z = Z statistic for a level of confidence (1.64 for 90% confidence level) [30]

The potential involvement of all employees and students attending medical, specialization and health professions degree courses, in the three university hospital centers involved in the project, will reasonably allow us to reach a higher sample size than the minimum target of 2,977 subjects. Indeed, for detecting an odds ratio (OR) as low as 1.69 (OR for male gender in [29]) with a type I error α=0.05 and power β=0.95, it would be required to reach a sample size of 3,503 subjects (z-test on logistic regression)

The calculation was performed using R statistical software (R Core Team, 2021).

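### The minimum target of 2,977 is the prevalence figure only; on the plan's own terms it does not carry the 95% power stated for the risk-factor objective

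*Protocol article*

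**What the plan says.** All of the relevant text is in the protocol article, Materials and methods, The sample size.

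- Purpose: "The sample size was calculated considering the objectives of estimating the prevalence of LTBI and identifying its risk factors".
- Prevalence inputs: "we assumed a prevalence of LTBI of 1% in our population", "an error estimate of d = 0.3" percent, and a Z value of "1.64 for 90% confidence level". Result: "we obtained a total sample size of 2,977 subjects to be enrolled".
- Target: involving all employees and students of the three centres "will reasonably allow us to reach a higher sample size than the minimum target of 2,977 subjects".
- Risk-factor inputs: "for detecting an odds ratio (OR) as low as 1.69 (OR for male gender in [29"), type I error 0.05 and power 0.95, by a z-test on logistic regression. Result: "it would be required to reach a sample size of 3,503 subjects".

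The Primary outcome and Secondary outcomes sections make prevalence primary and risk-factor identification secondary. The article does not say whether the 0.05 is one- or two-sided, what distribution the predictor has, or what share of participants is male.

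**The concern.** If one sample size is meant to serve two objectives, it has to be at least the larger of the two requirements. Here the term minimum target is attached to the smaller one. Any final number from 2,977 to 3,502 would satisfy the declared target and still fall below what the same paragraph says the risk-factor analysis requires.

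What is at stake is how the study will be judged. A report could state that the target was reached, and readers who recall the 95% would take it to apply at that number. It does not, even on the plan's own calculation.

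**Working it through.** **1. Reproduce 2,977.** Inputs from the article: P = 0.01, d = 0.003, 90% confidence. Formula: n = Z²P(1−P)/d².
- Z = 1.645: 1.645² × 0.0099 / 0.003² = 2,976.6, so 2,977. This reproduces.
- Z = 1.64 as printed: 2,958.6, so 2,959. This is a rounding difference of 0.6% and is not the issue here.

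**2. Reproduce 3,503.** Inputs from the article: OR 1.69 (b = ln 1.69 = 0.5247), risk 0.01, alpha 0.05, power 0.95. Assumed, because not stated: X ~ N(0,1), 1% risk at the mean of X, one-sided test. The formula is the Wald z-test for logistic regression with the null variance used for the alpha term:

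n = (z_α√v₀ + z_β√v)² / b²

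- Averaging the logistic risk over X gives an overall risk of 0.01142, so v₀ = 1/(0.01142 × 0.98858) = 88.59 and √v₀ = 9.412.
- The information matrix under the alternative gives v = 89.61 and √v = 9.466.
- n = (1.645 × 9.412 + 1.645 × 9.466)² / 0.5247² = 3,502.1, so 3,503. This reproduces exactly.

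Other settings tried do not give 3,503:

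| Setting (95% power) | n |
|---|---|
| Same method, two-sided | 4,204 |
| Hsieh formula, continuous predictor, one-sided / two-sided | 3,970 / 4,767 |
| Binary predictor split 50/50, one-sided | about 12,400–12,700 |
| Binary predictor split 50/50, two-sided | about 14,900–15,300 |

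**3. Power at 2,977 under the settings that reproduce 3,503.** Power = Φ[(√n·b − z_α√v₀)/√v].
- n = 3,503: (59.186 × 0.5247 − 1.645 × 9.412)/9.466 = 1.645, power 95.0%.
- n = 2,977: (54.562 × 0.5247 − 1.645 × 9.412)/9.466 = 1.389, power 91.8%.
- Without the null-variance term the two figures are 94.9% and 91.6%.
- Check without choosing a predictor model, by rescaling the stated 95% at 3,503: Φ[(1.645 + 1.645)√(2,977/3,503) − 1.645] = 91.7% one-sided. With 1.960 as the alpha quantile it is 91.4%.

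The gap is 3,503 − 2,977 = 526 subjects, 15.0% of 3,503.

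**4. Prevalence precision at each size.** Half-width = 1.645√(0.0099/n): 0.30% at 2,977 and 0.28% at 3,503. So 2,977 meets one of the plan's two criteria, and 3,503 nominally meets both.

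**5. The named factor is binary.** Assume 1% prevalence in the reference sex, 30–50% men, and a two-sided 0.05 Wald test. The risk in men is then 0.0169/(0.99 + 0.0169) = 1.68%. The standard error of the log odds ratio is √[1/(n(1−m)·0.01·0.99) + 1/(n·m·0.0168·0.9832)], where m is the male share.
- n = 2,977: power about 34–36%.
- n = 3,503: power about 39–41%.

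The male share and the reference risk are assumptions; the article gives neither.

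**The case against.** Four points can be made in the plan's defence.

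- **Hierarchy.** Prevalence is the primary outcome and risk factors are secondary. Taking the minimum from the primary outcome and printing beside it the larger number a secondary objective would need is a common and defensible layout. This stands, and it is why 2,977 cannot simply be called the wrong target. What remains is that the section opens by saying the size considered both objectives, and then never says that the minimum covers only one.
- **Openness.** The two figures appear in adjacent sentences, and the text expects to exceed 2,977. This also stands: nothing is hidden. But the expectation is not a commitment to 3,503, and a number in between would exceed the minimum and still miss the stated requirement.
- **No closing rule.** A reader might infer that enrolment will stop at 2,977. The documents do not support that: the Participants section invites all HCWs and students attending the annual visit, and the timeline runs by calendar date. The risk lies in how adequacy is reported, not in a planned early close.
- **Small loss.** About three points of power, with power still above 90%, is little. True on the settings that reproduce 3,503, but those settings are inferred.

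**Conclusion.** The point holds as a minor matter of how the target is stated. Both printed numbers can be reproduced, so neither is an arithmetic slip. The fault is that a paragraph claiming to size two objectives gives the minimum for one of them without saying so. At 2,977 the prevalence criterion is met, and power for OR 1.69 is about 92% instead of 95%. The 92% rests on a one-sided 0.05 test and a standard-normal predictor with 1% risk at its mean, neither of which the article states.

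Two stronger readings go beyond the documents. First, a reader might take about 92% (91.6% or 91.8%, depending on the variance term) as the true power at 2,977 for male sex. It is not: the cited odds ratio is for a binary factor, while 3,503 matches a continuous predictor. Under the assumptions in step 5 of the working, two-sided power for a binary factor is about 34–36%. Second, a reader might infer that raising the minimum to 3,503 cures the problem. It would restore only the nominal 95%; for the binary factor, power would be about 39–41% under the same assumptions.

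**What to change.** Restate the sample-size paragraph; no additional enrolment is needed. Say that 2,977 is the minimum for the primary outcome (prevalence) only, that the risk-factor objective is not sized at that number, and print the power at 2,977 with the test's sidedness, the type of predictor and the assumed male share.

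Alternatively, name the larger number as the single minimum for both objectives. Do this only after 3,503 has been recalculated with those three inputs stated; otherwise the plan would certify a figure that does not give 95% power for the factor it names.

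Cost: the first option is wording, plus a less favourable power figure in print. The second commits the study to at least 526 more subjects than the present minimum on the current figures, and to many more if the factor is treated as binary.

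The article says that changes affecting study objectives, design or population need a formal amendment. The first option clarifies which objective the existing number serves and changes no procedure; the second changes the declared minimum, so the sponsor should check whether it needs an amendment.

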### Participants

During the study period, all HCWs and students, who refer to Health Surveillance Unit of FPG/UCSC, UNIPA and to Unit of Occupational Medicine of University Hospital of Bari for the annual scheduled medical visit for judgment of suitability for work/activity, will be invited to participate to the study giving written informed consent. Participation in the study is proposed to all HCWs and students of three University Hospitals involved in the project (Fig 1). There are no other specific inclusion criteria. Exclusion criteria include known history of tuberculosis, previous chemoprophylaxis, positive tuberculin skin test (TST) performed within 12 months prior to enrollment and refusal of informed consent.

**Fig 1 pone.0319568.g001:**
[figure not shown]
Schedule of enrolment, interventions, and assessments.

## Procedures

### Primary outcome

The general objective of the research project is to develop an interoperable web-based platform to provide epidemiological and health surveillance against LTBI in the hospital setting. The primary outcome of the study is the prevalence of LTBI defined as 1) positive TST at enrollment, 2) tuberculin conversion defined as negative TST before enrollment and positive at enrollment, 3) subsequent positive QuantiFERON-TB Gold (QFT) test result performed on the same day as the positive TST result or within 5 days of tubulin conversion [higher response than the cut-off value of 0.35 IU/ ml of INF-γ was detected in at least one test tube (TB1 or TB2)], 4) chest imaging excluding pleural and/or pulmonary lesions suggestive of active tuberculosis and 5) final medical evaluation done by a Specialist in Infectious Diseases which excluded active disease. All five criteria must be met. One TST is scheduled for each participant. Furthermore, the study does not provide follow-up. Each participant continues regular annual follow-up as per routine clinical practice.

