**Fig 2 pone.0319568.g002:**
[figure not shown]
Health care workers and students questionnaire (English version). The specific 9 items self-test questionnaire, developed for the specific purpose and never administered before, administered to the enrolled HCWs and students.

The questionnaire was firstly validated through the following procedure

A Delphi Method structured on a panel of experts to achieve mutual agreement.The questionnaire was the object of a first validation phase on the first 25 responding subjects and results were analyzed to test its applicability and generalizability.

In addition to demographic information, a list of possible risk factors includes age and sex, Bacillus Calmette–Guérin (BCG) vaccination history, previous work or stay in other countries with high TB rates, known recent (within 6 months) exposure to TB-infected patient, current smoking, co morbidities/ medical history, median QuantiFERON-TB Gold In-Tube level (TB Ag-Nil) if available, occupation, working/ training Unit and years working as HCWs [32]. All positive QFT results on the first determination are repeated to confirm the finding. All conversions of QFTs are collected for the final analysis. No incentives will be offered to complete the survey. A first predictive model for LTBI will be set up through analysis performed by Real World Data GENERATOR.

All HCWs and students enrolled in UNIPA and in University Hospital of Bari will undergo the same methodologies adopted in FPG/UCSC.

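### The primary outcome is called LTBI prevalence, but its case rule makes tuberculin conversion compulsory, so a participant with no earlier negative TST can never be a case

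*Protocol article*

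**What the plan says.** The abstract states "The primary endpoint is the prevalence of LTBI". The Primary outcome section repeats this and gives five criteria:

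1. A TST that is positive when the person enrols.
2. "tuberculin conversion defined as negative TST before enrollment and positive at enrollment".
3. A positive QuantiFERON (QFT) result, "performed on the same day as the positive TST result or within 5 days of tubulin conversion" (the last phrase evidently means tuberculin conversion).
4. Chest imaging that rules out active disease.
5. A specialist's assessment that rules out active disease.

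The combining rule and the testing schedule follow directly: "All five criteria must be met. One TST is scheduled for each participant". The same section says that the study has no follow-up of its own.

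The Participants section invites all health-care workers (HCWs) and students at the three hospitals and sets no further entry condition. Four things exclude a person: known tuberculosis, earlier chemoprophylaxis, a positive TST in the preceding 12 months, and refusal of consent. An earlier TST is not required.

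**The concern.** Prevalence counts everyone who has the condition now, whenever it was acquired. A conversion requirement counts only those with an earlier negative test who are positive now. When both are compulsory, criterion 1 does no work and the outcome becomes QFT-confirmed conversion since some earlier negative test, over an interval that the protocol does not define.

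This affects more than the headline percentage. The same case status is the dependent variable in the logistic regression and the target of the machine-learning models (Statistical analysis), and it would carry into the validation cohort (Secondary outcomes). An infected person without an earlier negative TST would enter those models as a non-case. Whether a person can be counted would then depend on testing history, which plausibly differs by occupation and years worked. Both are candidate risk factors, so associations with them could partly reflect who had been tested before.

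**Working it through.** **Logical check.** Take an eligible participant with a positive TST at enrolment, a positive QFT, clear imaging and a specialist's exclusion of active disease.

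| Testing history | Criterion 1 | Criterion 2 | Case under the all-five rule |
|---|---|---|---|
| Earlier negative TST | met | met | yes |
| Never tested before | met | not met | no |
| Earlier TSTs all positive, none in the last 12 months | met | not met | no |

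All three are admitted by the Participants section. The study's single TST cannot supply the earlier negative result. No section reclassifies the second and third rows or removes them from the denominator.

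**The plan's own figure.** The sample size section uses n = Z²P(1−P)/d², with P = 1%, d = 0.3% and 90% confidence.
- Z = 1.645: 1.645² × 0.01 × 0.99 / 0.003² = 2,976.6, so 2,977. The stated figure is reproduced.
- Z as printed (1.64): 2,958.6, so 2,959. The difference is rounding of Z and does not matter here.
- Expected cases at 1%: 2,977 × 0.01 = 29.8, about 30.

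**Size of the effect (illustration).** Assumptions: true prevalence P = 1%; a share f of participants has an earlier negative TST; f is independent of infection; all infections in that group were acquired after that test; everyone enrolled is in the denominator. The protocol does not give f.

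Reported proportion = P × f; expected cases = 2,977 × P × f; bias = P × (1 − f).

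| f | Reported | Cases in 2,977 | Bias (points) |
|---|---|---|---|
| 25% | 0.25% | 7.4 | 0.75 |
| 50% | 0.50% | 14.9 | 0.50 |
| 75% | 0.75% | 22.3 | 0.25 |
| 90% | 0.90% | 26.8 | 0.10 |
| 100% | 1.00% | 29.8 | 0 |

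The bias stays within the planned margin when 1% × (1 − f) ≤ 0.3%, that is, f ≥ 70%. A larger sample does not reduce it.

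**Sensitivity to independence.** Let f = 50%.
- Prevalence 1.5% in those with an earlier negative TST and 0.5% in the rest (1% overall): reported figure 0.5 × 1.5% = 0.75%.
- The reverse pattern: 0.5 × 0.5% = 0.25%.

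So P × f is a central illustration and not a ceiling.

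**The case against.** The strongest reply is that most participants will have an earlier TST. The Introduction says that LTBI assessment is part of HCWs' annual surveillance, and the Participants section recruits at the annual scheduled visit. For established HCWs f may therefore be well above 75% and the bias small. This stands as a limit on the likely size. It does not remove the defect: f is not given, entry does not depend on it, and new staff and preclinical students are the least likely to have a record.

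A second reply is that the rule is a drafting slip. Criterion 3 times the QFT to a positive TST or to conversion, which suggests that criteria 1 and 2 were meant as alternatives. That is probably right. However, an alternative in a timing clause does not override the explicit instruction that all five apply, so the text still needs correcting.

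Several stronger readings are tempting, but the protocol does not support them.
- *Anyone with a positive TST more than 12 months ago is shut out.* Criterion 2 sets no interval and does not refer to the latest test. Someone negative five years ago, positive two years ago and positive now meets it. Only people with no earlier negative TST are shut out.
- *Uncountable people certainly stay in the denominator.* That is the natural reading, but it is not stated.
- *The result cannot be compared with the 2.1% and 0.62% used for planning.* The case definitions behind those rates are not shown.
- *The confirmatory QFT repeat conflicts with the case definition.* "All positive QFT results on the first determination are repeated to confirm the finding" is compatible with criterion 3. Which result decides is detail that a condensed article may leave to the full protocol.

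**Conclusion.** The point holds as an error in the stated case rule. It is not a gap left by condensing the protocol, because both the definition and the combining rule are given explicitly. Followed literally, the primary outcome does not measure the prevalence it names, because participants with no earlier negative TST have zero chance of being cases.

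If all enrolled participants form the denominator, the estimate is biased downward, and the misclassification passes into the risk-factor and prediction models. The direction follows from the logic alone. The size is illustrative only: it rests on the 1% planning prevalence, an unknown f, independence of f from infection, and infections acquired after the earlier test. Under those assumptions the bias exceeds the planned 0.3-point margin when f is below 70%, and it could be minor if nearly all participants have an earlier negative TST.

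**What to change.** Reconcile the combining rule with the named outcome. There are two coherent options.

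- **If prevalence is intended:** define a case as criteria 1, 3, 4 and 5, with conversion not required. Report conversion as a separate outcome whose denominator is participants with a documented earlier negative TST. Stating criteria 1 and 2 as alternatives gives the same cases, because every converter also meets criterion 1.
- **If conversion is intended:** rename the primary outcome, define the interval, and restrict the denominator to participants with a documented earlier negative TST.

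In either case, state the denominator and use the same case status in the regression and prediction models. Under the first option the estimate is still prevalence among eligible people only, because the exclusions for a recent positive TST and earlier chemoprophylaxis remain. The report should say so.

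The cost is an amendment of about a paragraph and re-derivation of case status. It may not be free of missing data: nothing in the protocol shows that TST-positive non-converters already enrolled had the QFT, imaging and specialist review. Check this at each site, and report those without the results as unclassified, not as non-cases.
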